### Data collection

The following data will be collected during the study. To guarantee the study quality, all the investigators will be trained and pass the examinations. The trained investigator (YW) who will be blinded to the allocation will collect intraoperative data. KL, QH, and QZ will do the anesthesia procedures and collect intraoperative data, respectively; to avoid bias, they will not participate in postoperative data collection. All the statistical analyses will be performed by one of the corresponding authors (YC).Demographic data: Age, BMI, ASA status, clinical diagnosis, history of spontaneous delivery, abdominal surgery history, and surgical index.Intraoperative data: The MAP and HR prior to induction (T0), at the time point of intubation (T1), 10 min after tracheal intubation (T2), surgical incision immediately (T3), 10 min after surgical incision (T4), 10 min before the end of surgery (T5), at the end of surgery (T6), and at the time point of tracheal extubation (T7); duration of surgery; duration of anesthesia; the consumption of anesthetics (including sufentanil and cisatricurium); consumption of vasoactive drugs (including nitroglycerin and metaraminol); intraoperative estimated blood loss. Intraoperative complications include bowel, ureter, and bladder injury.Postoperative data*Postoperative pain assessment* All patients will be guided to use a 0 to 10 cm visual analogue Scale (VAS) to express the degree of pain. VAS scores are collected at the time of 2 h after surgery and 24 h after surgery. Additional analgesic medications are available at the patient’s request. Number of patients who have a requirement for rescue analgesia are recorded. Postoperative rescue analgesia can be provided by intravenous injection of 5 μg sufentanil or ketorolac 30 mg.*Postoperative adverse events *The incidence of postoperative nausea and vomiting (PONV) during postoperative 24 h are recorded. Nausea is referred to the patient with uncomfortable feeling in their stomach, and the severity of nausea is evaluated as follows*:* none = 0, mild = 1, moderate = 2*.* If there is gastric content vomited out, it is scored as 3. Rescue antiemetic could be offered to any patient who has a nausea score > 2. Postoperative complications include surgical site infection within 14 days, and unplanned secondary surgery related to this surgery.

### Data management and confidentiality

The CRF is designed according to our protocol and deposited in our special safe. Only the study team member who has permission from the principal investigator has access to this safe. Data will be entered into an electronic database and double-checked by the third investigator (DF). Any missing data or errors in the data will be summarized along with detailed descriptions and will be queried by checking the original forms. When the study is completed, the key to safety will be preserved by the principal investigator (YC) who is one of the corresponding authors. The detailed identification of the enrolled patients will not be reported in publications.

### Data monitoring

Based on previous publications, we will not establish a data monitoring committee due to this trial is small-scale and conducted at a single center [11]. If severe adverse events occur during the procedure, such as cardiac arrest or severe bleeding associated with procedures, the principal investigator has access to these interim results and makes the final decision to terminate the trial. And unblinding is permissible. Any modification to the protocol will be discussed and agreed to by the study investigators and will be subsequently submitted to the CRB for approval. We will also update the protocol at the Chinese Registry of Clinical Trials.

### Outcome measures

1. The primary outcome is vital signs at the different time points, including before anesthesia (baseline: T0), at endotracheal intubation (T1), 10 min after endotracheal intubation (T2), at the beginning of the operation (T3), 10 min after the operation (T4), 10 min before the end of the operation (T5), at the end of the operation (T6) and at the time of tracheal extubation (T7).2. The second outcomes are collected as follows.①Surgical conversion rate refers to the surgeon cannot complete the surgery in the scheduled mode of operation, and has to convert to open abdominal surgery or traditional multiport laparoscopic surgery, or single port laparoscopic surgery. For the patient who is allocated to the gasless vNOTES group, the surgeon requires the use of traditional vNOTES with CO_2_ pneumoperitoneum if they are unable to complete the surgery under gasless vNOTES, and this patient is considered as a surgical conversion. If the operation cannot be completed according to the scheduled surgical method, the surgical strategy can be changed as appropriate.② Duration of surgery (from speculum placement to suturing the wound)③ Duration of anesthesia (from anesthesia induction to endotracheal extubation)④ The anesthetic consumption during the surgery, including sufentanil and cisatracurium⑤ Intraoperative estimated blood loss⑥ VAS and PONV scores at postoperative 2 h and 24 h.⑦ Administration of vasopressor drugs from the beginning of general anesthesia induction to 15 min after endotracheal intubation, including times, dosage, and type.⑧ Intraoperative and postoperative complications (e.g., bowel, ureter, and bladder injury, surgical site infection, and unplanned secondary surgery).⑨ Time of first getting out of bed after surgery⑩ Time of first eating after surgery after surgery, including light drink.

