## Background

Since Transvaginal Natural Orifice Transluminal Endoscopic Surgery (vNOTES) was applied and reported in 2007 by Marescaux et al., this technique has been increasingly conducted in the field of gynecology, such as hysterectomy [1, 2], adnexectomy [3], and myomectomy [3, 4]. Published literature has proved that, compared to traditional laparoscopic surgery, vNOTES hysterectomy is associated with a lower pain score after surgery and a shorter length of hospital stay [1]. Due to its minimally invasive and without abdominal incisions, maximum aesthetics can be achieved.

During the routine vNOTES procedure, carbon dioxide (CO_2_) pneumoperitoneum is required. CO2 insufflation may induce hemodynamic instability and acid–base imbalance. A well-summarized review has reported that acidosis, inflammation, oxidative stress, and hypothermia may all be associated with CO_2_ pneumoperitoneum [5]. Moreover, in an animal study, the authors found that an inflammatory response was evoked during pneumoperitoneum [6]. Additionally, the transvaginal insertion of devices to establish CO_2_ pneumoperitoneum makes the already narrow surgical space even more crowded, further exacerbating the inconvenience of transvaginal operations [7]. In 2014, Chen et al. performed the first transvaginal appendectomy under gasless laparoscopy [7]. Subsequently, they reported that transvaginal salpingo-oophorectomy with gasless laparoscopy was successfully conducted in ten patients [8]. However, technical difficulties associated with gasless laparoscopy, such as limited abdominal space and poor surgical visualization restrict its application.

To date, literature regarding the advantages of gasless vNOTES is insufficient. Most studies related to gasless vNOTES are case series, which is not convincing enough. Thus, the aim of our study is to compare gasless vNOTES vs. traditional vNOTES on hemodynamic profiles and outcomes in patients with benign gynecological disease. The primary outcome is the changes in mean arterial pressure (MAP) and heart rate (HR) at different time points during the surgery. The secondary outcomes will be surgical conversion rate and complications. We hypothesize that compared with those in the traditional vNOTES group, hemodynamic profiles will be changed less during gasless vNOTES, while safety can be promised.

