#### Intervention description

##### Anesthesia management and study intervention

The participants are continuously monitoring when they enter the operating room, including electrocardiograph (ECG), pulse oximetry, and non-invasive blood pressure. For the induction of the anesthesia, the patients are administered sulfentanyl (0.3 µg/kg), propofol (2 mg/kg), and cisatracurium (0.15 mg/kg) intravenously. Then, sevoflurane is adjusted for maintaining anesthesia and achieving a target BIS between 40–60 during the surgery. A single injection of sulfentanyl (0.1 µg/kg) and a bolus dose of cisatracurium (0.05 mg/kg) are permitted to be given independently during the surgery if necessary. When the surgery is completed, the patients are reversed with neostigmine 0.04 mg/kg and atropine 0.02 mg/kg if their TOF ratio is less than 0.9. Tracheal extubation is performed after the patient is fully awake and follows instructions.

If the patient’s MAP decreases > 20% compared to the baseline, the patient is given an intravenous injection of phenylephrine 40 µg. If the patient’s HR is detected to be less than 50 bpm, atropine will be given 0.3 mg per time. In the case when MAP increases to more than 30%, nitroglycerin 100 µg per time is administered.

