### Sample size estimation

The sample size calculation was based on the changes in patients' blood pressure at the beginning of surgery. Since no similar studies have been conducted before, a pilot study was conducted previously. According to the results of the pilot study, in the traditional vNOTES group, 50% of patients had a greater than 20% change in blood pressure at the beginning of the CO_2_ pneumoperitoneum. Due to the different surgical strategies, CO_2_ pneumoperitoneum is not required in the gasless vNOTES group. We assume that the number of patients with a blood pressure change of more than 20% is less in the gasless vNOTES group than in the traditional vNOTES group. The 10% reduction in the gasless vNOTES group was considered to be statistically significant. A statistical power of 80% and a one-sided α significance level of 0.05 were used for power analysis with 1:1 allocation. A sample size of 49 patients in each arm was estimated. Considering a dropout rate of 20%, 60 patients for each group were enrolled.

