## Discussion

This is the first randomized controlled trial to compare the impacts of gasless vNOTES vs. traditional vNOTES on hemodynamic profiles and outcomes in patients with benign gynecological disease. It is noted that pneumoperitoneum and carbon dioxide insufflations which are required during traditional vNOTES may lead to an increase in plasma catecholamine levels and plasma renin activity. Besides, the increased intra-abdominal pressure may lead to reduced thoracic and pulmonary compliance. All these changes result in an increase in heart rate, blood pressure, and reduced cardiac output. Moreover, a systematic review has well-summarized the “dark” disadvantages related to pneumoperitoneum effects, such as leading inflammatory response, inducing acidosis, producing reactive oxygen species, and adhesion development [5]. However, CO2 insufflation can provide a better visualization of the surgical field, which may shorten surgical duration and decrease surgical-related complications. If a favorable effect and safety of gasless vNOTES for hemodynamic profiles and outcomes in patients are shown, gasless vNOTES would be an optimal treatment option for patients with benign gynecological disease. Additionally, previous studies have proved that the use of vNOTES may be particularly effective and safe for selected populations, such as obese women, and women with large uteri [12, 13]. In our study, we may find that the application of gasless vNOTES is suitable for patients with abnormal cardiopulmonary functions.

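### The only declared baseline precedes anaesthesia while change is judged without sign, so an induction fall could offset the expected CO2 rise; the reference, sign and adjustment need fixing

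*Protocol article*

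**What the plan says.** All places are in the protocol article.

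- **Outcome measures** gives the primary outcome as vital signs at T0 to T7, "including before anesthesia (baseline: T0), at endotracheal intubation (T1" and onward. No other reading is called baseline. **Data collection** confirms the timing: "The MAP and HR prior to induction (T0".
- **Background** describes the outcome as a change: "The primary outcome is the changes in mean arterial pressure (MAP) and heart rate (HR) at different time points during the surgery". It hypothesises that "hemodynamic profiles will be changed less during gasless vNOTES".
- **Sample size estimation** rests on a pilot in which, in the traditional arm, "50% of patients had a greater than 20% change in blood pressure" when pneumoperitoneum began. It does not say what that change was measured from, or in which direction.
- **Discussion** gives the expected effect of CO2: "All these changes result in an increase in heart rate, blood pressure, and reduced cardiac output".
- **Anesthesia management and study intervention** describes the same induction for all patients and provides for the case where "MAP decreases > 20% compared to the baseline".
- **Surgical technique** starts CO2 after the port is inserted, hence after induction. **Data collection** schedules a reading between the two: "10 min after tracheal intubation (T2".
- **Statistical methods** names a t-test or a non-parametric test for the primary outcome, with no covariate. It does not say whether levels, signed changes or absolute changes are compared.

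**The concern.** Two influences act on MAP between T0 and the operative readings. Anaesthesia acts in both arms, and the protocol provides for falls from it. CO2 acts in one arm, and the protocol expects it to raise pressure. A rise on top of a fall brings MAP back towards T0. If less change is judged by distance from T0, the CO2 arm can look the more stable one because CO2 moved its pressure. The trial could then miss a true CO2 effect or report it with the wrong sign.

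The protocol's own wording invites that reading: T0 is the only baseline, and both the hypothesis and the sizing criterion ignore direction. Separately, the stated unadjusted test makes no use of the T0 value that is collected on every patient.

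**Working it through.** **Inputs from the document (directions only).** The reference is T0. Anaesthesia may lower MAP in both arms. CO2 raises it in one arm, after induction. The criterion is an absolute change above 20%.

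**Inputs assumed.** Mean anaesthetic fall F, mean CO2 rise C and SD, all in % of T0. The document gives none of these, so ranges are used: F 0 to 25, C 10 to 30, SD 10 and 15.

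**Model.** Change from T0 is normal with the same SD in both arms. The mean is −F in the gasless arm and −F + C in the traditional arm. For mean m,

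P(m) = 1 − [Φ((20 − m)/SD) − Φ((−20 − m)/SD)].

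**General result.** P(m) depends only on |m| and increases with it. The arms are therefore equal when |C − F| = F, that is F = C/2. When F > C/2 the gasless arm has the higher rate, whatever the SD.

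**Numbers for C = 20, SD = 15.** For a post-induction reference, the gasless mean becomes 0, and C and SD are divided by (1 − F/100).

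| F | From T0: traditional vs gasless | Difference (points) | From a post-induction value: difference (points) |
|---|---|---|---|
| 0 | 50% vs 18% | +32 | +32 |
| 5 | 38% vs 21% | +17 | +33 |
| 10 | 28% vs 28% | 0 | +33 |
| 15 | 21% vs 38% | −17 | +33 |
| 20 | 18% vs 50% | −32 | +33 |
| 25 | 21% vs 63% | −43 | +32 |

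Example for F = 20: the traditional mean is 0, so P = 2 × Φ(−20/15) = 2 × 0.091 = 18%. The gasless mean is −20, so P ≈ 50%.

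**Other values at F = 10, from T0, SD 15.** C = 10 gives −9 points, C = 15 gives −7, C = 20 gives 0 and C = 30 gives +23. The sign turns at C = 2F = 20, as the general result says.

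**Unequal SDs.** Take SD 12 for the induction change, 8 for reading noise and 10 for the CO2 effect. The gasless SD is √(144 + 64) = 14.4 and the traditional SD is √(144 + 64 + 100) = 17.5. With F = 20, C = 15 the rates are 27% vs 50%. With F = 10, C = 15 they are 27% vs 26%.

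**The pilot's 50%.** With these unequal SDs, no fall and a 20% rise gives 51% vs 17%. A 25% fall and a 5% rise gives 51% vs 64%. The same traditional rate fits a strong contrast in the expected direction and a reversed one, so the pilot figure does not settle which applies.

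**Signed or level comparison.** The expected difference at one time point is (−F + C) − (−F) = C. The fall cancels.

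**Adjustment.** Adjusting for a covariate with correlation r multiplies the residual variance by 1 − r². For assumed r of 0.5 and 0.7 that is 0.75 and 0.51, a cut of 25% to 49%. The document gives no correlation, and that of T0 with an anaesthetised reading may be lower.

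**The case against.** The strongest reply is that the article never defines change as Tx minus T0. Outcome measures simply lists vital signs at time points, and baseline may be no more than a label in that list. If Statistical methods means levels or signed changes compared at each time point, randomisation makes the induction fall common and it cancels. This stands. A reader might infer that the plan has fixed a wrong reference and that the comparison will be biased; the document does not support that.

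Nor is change above 20% a listed endpoint. It appears only in the sample-size text, where the timing given could mean change around insufflation. This also stands, so the table shows what one open reading would do and not what the plan prescribes.

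The model is simple as well. It gives the gasless arm no response to incision or wall lifting, and it ignores treatment triggered by a fall from baseline, which would limit recorded falls. These affect the sizes but not the mechanism.

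A reader might further infer that T3 is the natural reference, because it is the last reading near the start of CO2. It is a poor choice: it carries the immediate incision response, and the sample size was based on the beginning of surgery. Estimates against T3 are also easily overstated. With C = 15 and the unequal SDs above, counting reading noise once gives 35% vs 1%; counting it in both readings gives 38% vs 8%.

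Departure from a patient's own awake value is a legitimate measure, and T0 is the only reading before drugs and surgery. That is a reason to keep reporting it. It does not remove the need to state sign and reference.

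**Conclusion.** The point holds conditionally. With T0 as the only declared baseline and unsigned wording in both the hypothesis and the sizing criterion, an unsigned change from T0 can shrink, hide or reverse the CO2 contrast. Under the equal-SD normal model it reverses once the induction fall exceeds half the CO2 rise. In the example it runs from +32 points with no fall to −32 points with a 20% fall. F, C and SD are assumptions throughout.

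A signed or level comparison is free of this bias. Its interpretation is still exposed, because a higher MAP nearer T0 in the CO2 arm could be read as having changed less. The unadjusted t-test is valid but ignores the collected T0. The choice should be written down before analysis, because choosing the reference afterwards could choose the result.

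**What to change.** 1. Compare MAP and HR between arms as signed differences at T4 and T5, by ANCOVA or a mixed model adjusting for T0, in place of the unadjusted t-test. With T0 as covariate, the arm difference is the same whether the outcome is the level or the change from T0, which removes that ambiguity.
2. State in advance how each sign will be read against the hypothesis, so that a return towards T0 under CO2 is not counted as stability.
3. Define any measure of change above 20% from T2, which follows induction and precedes incision and CO2, and state its direction. Report change from T0 alongside it. Do not use T3 as the main reference.
4. Reconcile the wording of T4: Data collection times it from the incision, while Outcome measures words it as after the operation.

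**Cost.** Analysis wording only; every reading is already scheduled.

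**Downside.** T2 is post-randomisation, is read when the theatre team may know the allocation (the envelope goes to the surgeon), and lies within the window in which vasopressor use is recorded, so it may be modified by those drugs. The T0-referenced result should therefore be kept as a sensitivity analysis.

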**Methods:**

This is a single-center, prospective, single-blind, randomized controlled clinical trial, which has been approved by the Institutional Review Board of Chengdu Women’s and Children’s Hospital on September 27, 2022. One hundred and twenty patients will be recruited and randomly assigned to either the traditional vNOTES group or the gasless vNOTES group in a 1:1 ratio. For patients allocated to the traditional vNOTES group, after insertion of one port through the vagina, CO_2_ gas is infused with a pressure of 12–14 mmHg; while for those allocated to the gasless vNOTES group, a special device is used as an abdominal wall-lifting device to facilitate gasless surgery. CO_2_ pneumoperitoneum will not be used during the whole gasless vNOTES procedure. The primary outcome is vital signs at different time points. The secondary outcomes include surgical conversion rate, duration of surgery and anesthesia, anesthetic consumption, intraoperative estimated blood loss, VAS and PONV scores at postoperative 2 h and 24 h, administration of vasopressor drugs from the beginning of general anesthesia induction to 15 min after endotracheal intubation, including times, dosage, and type, intraoperative and postoperative complications, time of first getting out of bed after surgery, and time of first eating after surgery, including light drink.

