##### Surgical technique

Since surgical proficiency may be one of the major potential influenced factors affecting the outcomes, all surgeries are performed by the specialist surgeons with more than 3 years of experience in performing vNOTES. All patients are placed in the lithotomy position. Standard vaginal and abdominal preparation is performed in all of our patients in case of conversion to transabdominal surgery. A Foley catheter is inserted to drain the urinary during surgery. The vaginal incision is made around the cervix.

For patients who allocate to the traditional vNOTES group, after insertion of one port through the vagina, CO_2_ gas is infused with a pressure of 12–14 mmHg. A 10-mm rigid 0°laparoscope is used, and energy devices to coagulate and remove the diseased tissue according to the location of the lesion. After the procedure is completed, vaginal cuff closure is done extracorporeally with continuous locking suture with 1–0 vicryl.

For patients who are allocated to the gasless vNOTES group, a special device is used as an abdominal wall-lifting device. One point is placed at the adnexa surface projection on the abdominal wall to establish the operating space, and the other point is placed under laparoscopic observation to facilitate gasless surgery. CO_2_ pneumoperitoneum will not be used during the whole procedure (Fig. 1).

After the surgery, patients will be transferred to the post-anesthesia care unit (PACU).

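### The vasopressor outcome closes 15 min after intubation, so by the listed time points at most about 5 min of it, and possibly none, falls after the arms differ

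*Protocol article*

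**What the plan says.** The Outcome measures section of the protocol article lists as its seventh secondary outcome "Administration of vasopressor drugs from the beginning of general anesthesia induction to 15 min after endotracheal intubation", with the times, dose and type of drug to be recorded. The Methods paragraph of the abstract repeats the same window, so it is not a slip in one place.

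The Data collection section gives the order of the measurement points: "10 min after tracheal intubation (T2), surgical incision immediately (T3), 10 min after surgical incision (T4". Under Surgical technique, CO2 in the traditional arm is infused only "after insertion of one port through the vagina". In the gasless arm the wall-lifting device is placed during surgery to create the operating space. The Anesthesia management section describes induction once, with no distinction by arm.

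On drugs, the same section gives three rescue rules. For a fall in MAP, "the patient is given an intravenous injection of phenylephrine"; atropine is named for low heart rate and nitroglycerin for raised MAP. The Data collection section lists, as intraoperative data and with no 15-minute limit, "consumption of vasoactive drugs (including nitroglycerin and metaraminol").

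**The concern.** The arms differ in one thing: how the operating space is made. Sample size estimation places the expected blood pressure effect at the start of CO2 pneumoperitoneum, and the Discussion attributes the haemodynamic changes to insufflation and raised intra-abdominal pressure. An outcome meant to compare drug support between the arms should cover that period. This one is anchored to intubation and appears to end at about the time that period begins.

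Two things are at stake. First, rescue drugs are triggered by changes in MAP and heart rate, which are the primary outcome. Treatment pulls those readings back toward baseline, so drug use during the exposed period is needed to interpret similar MAP and heart rate curves. Second, a null result on this outcome could be misread as evidence that the two techniques need equal haemodynamic support, when it would mostly reflect equal induction.

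**Working it through.** The plan states no figure for this point, so there is none to reproduce. The check is arithmetic on the timeline, followed by a comparison of the drug lists.

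**Inputs**
- Window end: 15 min after intubation (Outcome measures; abstract).
- T2: 10 min after intubation. Incision, T3, is listed after T2, so x, the minutes from intubation to incision, is at least 10 (Data collection).
- T4: 10 min after incision (Data collection).
- y, the minutes from incision to CO2 or wall lift: not stated. Assumed range 0 to 10.

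**Overlap.** Minutes of the window with the arms different = max(0, 15 − (x + y)).

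| x (min) | y = 0 | y = 3 | y = 5 | y = 10 |
|---|---|---|---|---|
| 10 | 5 | 2 | 0 | 0 |
| 12 | 3 | 0 | 0 | 0 |
| 15 | 0 | 0 | 0 | 0 |
| 20 | 0 | 0 | 0 | 0 |

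The largest value, 5 min, needs the earliest incision that the listed order allows and exposure at the instant of incision. From intubation to the close of the window is 15 min, so 5/15 is one third. The window also includes the time from induction to intubation, so the exposed share of the whole window is below one third even in this best case.

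**Later time points.** T4 falls at x + 10, so at least 10 + 10 = 20 min after intubation. The window has closed by then. Drugs given around T4, or later up to the end of surgery, do not count.

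**Drug lists**

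| Drug | Named in rescue rules | Named for collection |
|---|---|---|
| Phenylephrine | yes | no |
| Atropine | yes | no |
| Nitroglycerin | yes | yes |
| Metaraminol | no | yes |

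One drug of four appears in both sections. In addition, the outcome is worded for vasopressors, whereas the Discussion expects heart rate and blood pressure to rise under pneumoperitoneum. The rescue rule for raised MAP names nitroglycerin, which is not a vasopressor, so the outcome's wording leaves it out.

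**The case against.** The quoted facts are not in dispute. The case on the other side is about how far they reach, and much of it stands.

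- A reader might infer that the outcome cannot show a difference at all, or is null by design. The documents do not support that. They give no minutes from intubation to incision, or from incision to insufflation or lift, so up to about 5 min of overlap remains possible on the listed order.
- A reader might infer that the drug mismatch means rescue doses will go unrecorded. That does not follow. The collection list is introduced as including two drugs, which is not exhaustive, and the outcome records drug type. The mismatch is an inconsistency between two sections and is not a cause of the window problem.
- A reader might infer that this outcome is the only way to tell stable patients from treated ones. It is not. Intraoperative vasoactive consumption is already listed without the 15-minute limit, and nitroglycerin is named there. The defect is that the declared outcome does not use those data.
- The outcome is one of ten secondary outcomes and does not enter the sample size. The primary outcome follows MAP and heart rate through to extubation. This limits the weight of the point.
- Simply extending the window would bring its own bias. The Discussion says CO2 may shorten surgery, so total dose could differ because duration differs. Starting the clock at insufflation or lift would use a different event in each arm, and gasless patients converted to CO2 would have two such starts. The fix has to deal with this.

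What remains is that the window is stated explicitly, twice, and covers almost none of the period in which the arms differ. That is a choice the protocol has fixed, so it is not a detail left to an analysis plan.

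**Conclusion.** The concern holds in this form: the seventh secondary outcome mainly compares vasopressor use during identically described induction and can hardly show a treatment difference. At most about 5 min of its window, and possibly none, falls after the arms diverge.

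This rests on two assumptions. Incision follows T2, as the listing implies; a patient incised sooner would have more overlap. And exposure begins no earlier than incision, which the port-insertion step supports for CO2 and which is taken to hold for the wall lift as part of surgery. The range for y is assumed, but the 5-minute ceiling does not depend on it.

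The difference in named drugs is a separate, minor inconsistency. The change is worth making, at a weight suited to a secondary outcome.

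**What to change.** Redefine the outcome as all vasoactive drugs given, with type, number of doses and total dose, from incision (T3) to the end of surgery (T6). Both points are already recorded in both arms, so the clock is the same for everyone, including converted patients. Use the intraoperative consumption data already listed.

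- Analyse by allocated arm, so that gasless patients converted to CO2 stay in the gasless arm.
- Report the proportion of patients receiving any drug, and use per unit of operating time, because duration may differ by arm.
- Report use from induction to incision separately, as a descriptor of the period before the arms differ.
- Have the investigators reconcile the drugs named under Anesthesia management with those under Data collection, and make collection cover every agent actually given. This review takes no position on which agent is right, and no change to treatment is proposed.

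The cost is small but not nil. Recruitment began in October 2022 and was due to finish in March 2024, so this is an amendment during the trial, with review board approval and a registry update as set out under Data monitoring. For patients already treated, drug timing relative to incision must come from existing anaesthesia records where available. Report the number of patients for whom it cannot be recovered, by arm.
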